#### Baseline Assessment

At baseline, sociodemographic data (i.e. age, gender, education level, social status, occupation and work status, past medical history, LBP history), and any previous treatment for LBP will be recorded, while blood pressure, body mass index (BMI, kg/m^2^), and cardiorespiratory fitness using the shuttle walk test [46], will be measured by the Trial Co-ordinator. In addition, participants will be questioned about sleep specific factors which have been reported in the literature to influence sleep quality i.e. sleeping place (e.g. bed, chair), environmental noise (e.g. trains, airport, motorway), mattress firmness and bed-time, bed sharing, smoking, alcohol or caffeine consumption, painkillers/sleeping tablet use [8,47-53]. Each participant will also be asked to indicate their view on the primary reason for their sleep disturbance.

*Sleep quality *will be measured using three validated self-report measures (the Pittsburgh Sleep Quality Index [31] the Insomnia Severity Index [32] and the Pittsburgh Sleep Diary [54] and a validated objective measure, the Actiwatch [30].

#### Pittsburgh Sleep Quality Index (PSQI)

This is a widely used retrospective questionnaire which assesses sleep quality and disturbance over the last month [31,55-57]. Nineteen individual items generate seven "component scores" (e.g. participantive sleep quality, sleep latency, sleep duration, sleep efficiency, sleep disorders, use of hypnotics, and poor daytime functioning). Summation of these scores ('0' no difficulty-'3' severe difficulty) yields a global score (range 0-21) that indicates a participants' participantive sleep quality (score of >5 points indicative of sleep disturbance). The PSQI has a sensitivity of 89.6-98.7% and a specificity of 84.4-86.5% for identifying cases with a sleep disorder, when the cut-off score of >5 points is used. The PSQI will be the main outcome measure of sleep disturbance.

#### Insomnia Severity Index (ISI)

This questionnaire has been designed with reference to the Diagnostic and Statistical Manual for Mental Disorders (DSM-IV) criteria for insomnia and is a reliable and valid measure containing seven items to quantify perceived insomnia severity (initial, middle, terminal), dissatisfaction with current sleep pattern, interference with daily functioning, noticeability of sleep impairment attributable to the sleep problem, and degree of distress or concern raised by the sleep problem [32,58]. The statements are scored on 4-point Likert-scales ('0' not at all - '4' extremely) generating a total score (range 0-28), indicating clinical insomnia severity (0-7 points no clinically significant insomnia; 8-14 points subthreshold insomnia; 15-21 points clinical insomnia (moderate); 22-28 points clinical insomnia (severe)).

#### Pittsburgh Sleep Diary (PSD)

This is a widely used instrument with eight components, five of which are completed at bedtime and relate to the events of the day preceding the sleep (e.g. alcohol, caffeine, medication consumption, exercise, 'lights out'), and three which are completed on wakening that relate to the sleep period just completed (final wakening time, number of awakenings, sleep quality) [54]. Participants will be instructed to report every item every day for 7-nights at baseline (starting on day of recruitment) and at 3 and 6 month follow-up.

#### Actiwatch (Model AW4, CamNTech, Cambridge, UK)

This is a small wrist-mounted device (37 × 29 × 10 mm; 16 grams), worn on the non-dominant wrist, which detects and logs movement intensity and duration by means of a small piezo-electric accelerometer. Using sleep analysis software it is capable of evaluating sleepwake patterns and common sleep quality variables: i.e. sleep onset latency, sleep efficiency and sleep fragmentation. It has been extensively validated against polysomnography, the 'gold standard' for sleep studies in healthy participants [59-62] and those with sleep disorders [63-65]. The Actiwatches will be set to average activity count data during recording at 10-sec epochs. Each participant will be requested to wear the Actiwatch on two separate occasions each lasting 7 nights as recommended by the American Academy of Sleep Medicine [66] at (i) baseline (starting the first night of recruitment), and (ii) 3 month follow-up either all day or from at least 30 min before they go to bed until at least 30 min after they wake up. After each 7-night period of sleep recording, participants will return the device to Beaumont Hospital in person or by courier, where data will be downloaded for analysis using the USB Actiwatch-reader and the Actiwatch Sleep v7.27 analysis software (CamNTech, Cambridge, UK). Before analysis, actigraphic data will be automatically converted to 30-sec epochs by the software and all sleep episodes will be visually inspected (scale: 1000) to screen for malfunctioning of the devices and non-wear time.

#### Oswestry Disability Questionnaire

This is a valid and reliable measure of functional disability due to low back pain [67]. It consists of ten items, which measures participants levels of functioning/disability in various activities of daily living. Each item contains six statements (0-5 points), of which one has to be chosen. The total score is converted into a percentage score (Oswestry Disability Index, ODI) [68] with 0-20% indicating minimal disability, 21-40% moderate disability, 41-60% severe disability, 61-80% crippled and 81-100% total incapacitation.

The ODI will be the main outcome measure of LBP-related disability.

#### Numerical Pain Rating Scale

This is a widely used valid and reliable measure of pain, whereby participants will be requested to choose a number from 0 (no pain) to 10 (worst possible pain) that best describes each of the following symptoms: current and average pain for both back and leg pain [69].

#### Short-Form 36 Version 2 questionnaire (SF-36v2)

The SF-36v2 (SF-36 Medical Outcomes Trust, Waltham, MA, USA) [70], is a 36 item valid and reliable measure of health-related quality of life. It yields an eight scale profile of functional health and well-being score of which two standardised summary scores (i.e. Physical Component Score [PCS] and Mental Component Score [MCS] are calculated.

#### Fear-Avoidance Beliefs Questionnaire (FABQ)

This is a 16 item (0-6 scale per item) self-report questionnaire that focuses on participants beliefs about how physical activity (5 items; 0-30) and work (11 items; 0-66) affect their low back pain [71].

#### Hospital Anxiety and Depression Scale (HAD)

This is a widely used self-report questionnaire for detecting overall states of anxiety and depression in non-psychiatric medical contexts [72]. It consists of 14 items which are statements to be scored on 4-point Likert-scales (0-3), generating 'Anxiety' or 'Depression' scores ranging from 0 to 21 (total score = 0-42); which are categorised as a "non-case" (0-7 points), a "borderline case" (8-10 points) or a "case" (≥11 points).

#### International Physical Activity Questionnaire (IPAQ)

This is a self or telephone-administered physical activity recall questionnaire, which will ask participants about the time they spent being physically active in the previous seven days. It has been found to be a valid method for monitoring population levels of physical activity globally for populations of 18-69 years of age [73].

#### Exercise Self Efficacy Questionnaire

Participants will be requested to rate their confidence in exercising under five different situations (i.e. when tired, in a bad mood, limited time, on holiday, bad weather) on five point Likert scales ranging from 'not at all confident' to 'extremely confident' [74].

#### Readiness to Change Questionnaire

Participants will be requested to state their current level of physical activity participation from one of five possible responses ranging from 'I currently do not exercise and I do not intend to start exercising in the next 6 months' to 'I currently exercise regularly and have done so for longer than 6 months' [75].

#### Employment status

The employment status of all participants (employed, homemaker, carer, unemployed, student, retired, disability) and current work status (working, sick leave) of those in paid employment only will be recorded at each follow-up point.

#### Patient Satisfaction Questionnaire

This questionnaire utilises Likert scales to assess participant satisfaction with outcome and satisfaction with physiotherapy care during the trial and will be administered at the 3 month follow-up point only [76]

#### Devices Utility Questionnaire

This is 7-item questionnaire designed to establish the utility (user-friendliness and its difficulties) of the objective sleep measures, adapted from a previously developed questionnaire [77]. Acceptability as a sleep measure, interference with sleep, wearing comfort, and awareness of wearing the device will be scored on 11-point numerical rating scales from 0 (not acceptable) to 10 (very acceptable). Participants will be requested to provide any free text comments on the use of the objective measures.

Participants will be phoned to request attendance at a face to face follow-up in the physiotherapy department at 3 months, and pre-paid postage envelopes will be sent at 6 months. Follow-up reminders will be given by phone and letter. Non-responders to the 3 month face to face follow-up will be requested to return completed questionnaires by pre-paid post or by telephone. A courier will be available to return the sleep monitoring devices unreturned by patients during the trial.

### Interventions

#### (i) Supervised exercise class (SEC)

Within one week of randomisation, participants will commence the SEC. This class will follow a group-based format based on the 'Back to Fitness' programme used in the UK BEAM trial [37] which is underpinned by cognitive behavioural therapy principles designed to change participants behaviour by modifying their attitude to their LBP, i.e. 'hurt' does not mean harm [78,79]. First, each participant will attend the physiotherapy department for an initial individual assessment with the Chartered Physiotherapist delivering the class, where there will be discussion and agreement between the therapist and the patient on short and long-term goals; recording of the patient's exercise capabilities and perceived barriers to recovery and the individual's treatment expectations. Second, participants will attend the physiotherapy department of the relevant participating hospital once a week for 8 weeks for a one-hour supervised group exercise class led by a Chartered Physiotherapist. The physiotherapist will advise patients according to their individual goals and exercise capabilities, and help identify which exercise(s) they could continue independently of the treatment sessions, i.e. foster the development of self-management strategies. Participants will also be required to rate their perceived exertion during the class on the Borg scale - a linear scale measuring level of breathlessness from 0 = 'not breathless at all' to 10 = 'maximal' [80,81]. Patients will be encouraged to accept responsibility for determining and carrying out their weekly programme of activity. Adherence with the supervised exercise programme will be recorded as the number of sessions attended. The number of sessions defined as adherence will be decided on completion of the trial.

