Participants will then be contacted once per week by telephone by the Chartered Physiotherapist who performed the initial assessment to progress their walking frequency and duration based on their exercise diary record of the previous week's walking, and to provide encouragement. These telephone calls will be based around a telephone script based upon CBT principles, adapted from a previously developed telephone script for another LBP clinical trial [88]. Participants will be advised that just like athletes, any unaccustomed exercise is likely to produce some muscle soreness [79]. Participants will be advised to use their pedometer [89] as a motivational feedback tool, providing immediate information on activity levels [90].

Adherence with the walking programme will be assessed by the frequency, distance, number of steps taken and duration of walks recorded in the exercise diary. Specific adherence levels will be established once the trial is complete. At the end of the intervention participants will re-attend the physiotherapy department for a review appointment with a view to discharge from physiotherapy.

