#### (iii) Usual Physiotherapy (UP) -Control Group

Within one week of randomization, participants will commence individual usual physiotherapy at the discretion of the treating physiotherapist. All physiotherapy treatments and the number of visits will be recorded for the study period in previously designed treatment record forms. On the basis of a previous RCT by the Principal Investigator in the Republic of Ireland public physiotherapy health service the anticipated mean (SD) number of treatments is 5.8 over a mean (SD) of 7.7 weeks (5.8) weeks [91]. A multimodal approach of education/advice, manipulative therapy and exercise therapy will be permitted on the basis of the results of previous surveys of physiotherapy practice in the UK and Ireland [25-28]. As part of this it is expected that participants will be provided with an individualized exercise programme at the discretion of the treating therapist but will not be permitted to attend group exercise classes or undertake a walking programme during the trial. Adherence will be assessed by the number of visits prior to discharge from physiotherapy.

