### Data Analysis

All data will be coded and entered into the Statistical Package for the Social Sciences database for analysis following data cleaning and checking for errors. Since this is a feasibility study extensive exploratory analysis of the data will be undertaken. Treatment effects will be represented by point estimates and confidence intervals of all outcome variables at all follow-up points. Means and standard deviations will be used to calculate effect sizes for the main outcome variables (i.e. PSQI, ODI), and to undertake a power calculation for the main trial. Monthly recruitment rates and ratio of number screened: number enrolled will be tabulated. This information will be used to help select the recruitment period and number of centres for the main study. The assessment of patient satisfaction will be tabulated, as will adherence levels, any recorded difficulties experienced with the protocol, including the use of the sleep monitoring equipment or adverse events experienced by the patients or therapists. The following criteria would suggest that a main trial is not feasible: no apparent change in the outcomes with confidence intervals that include large negative values, feedback from participants that they were unable/unwilling to complete the outcome measures or adhere to the intervention, high level of adverse events.

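### Active-arm adherence cut-offs are to be chosen after the trial is complete, and the control arm's adherence measure is a visit count with no denominator

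*Protocol article*

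**What the plan says.** The protocol article defines adherence separately in each arm, under Interventions.

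- **Supervised exercise class (SEC).** After an individual assessment, participants attend "once a week for 8 weeks for a one-hour supervised group exercise class". The measure is a count: "Adherence with the supervised exercise programme will be recorded as the number of sessions attended". The cut-off is deferred: "The number of sessions defined as adherence will be decided on completion of the trial".
- **Walking programme (WP).** "Adherence with the walking programme will be assessed by the frequency, distance, number of steps taken and duration of walks recorded in the exercise diary". Again the cut-off is deferred: "Specific adherence levels will be established once the trial is complete". The section states a programme aim of 30 minutes of moderate walking on five days a week by week five, maintained to the end of the eight weeks.
- **Usual physiotherapy (UP).** "participants will commence individual usual physiotherapy at the discretion of the treating physiotherapist". The article anticipates a mean of 5.8 treatments but prescribes no number. "Adherence will be assessed by the number of visits prior to discharge from physiotherapy".

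The quantitative Data Analysis section says that adherence levels will be tabulated. It lists three signs that a main trial would not be feasible. One is feedback from participants that they were "unable/unwilling to complete the outcome measures or adhere to the intervention". None of the three signs carries a numerical threshold.

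The Blinding section says that the outcome assessor will not be blinded in this study. It mentions blinding of the assessor and the statistician only for a future main trial.

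**The concern.** There are two separate problems.

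**Timing in the active arms.** The article does more than leave adherence undefined, which could be put down to a fuller document that is not shown. It commits to fixing the cut-offs after the data exist. By then attendance, diaries and outcomes are all known, and no blinding protects the choice. A statement that a certain percentage of participants adhered would then depend partly on a choice made with the result in view. In a feasibility study that percentage is one of the results a main-trial team will look for.

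**Meaning in the control arm.** A visit count can be read as adherence only against a planned or booked number. Here the therapist decides how many visits there are. A low count may mean quick recovery and planned discharge, or it may mean that the patient stopped coming. These have opposite implications for whether the arm can be delivered. If booked visits and the type of discharge are not captured during treatment, they may be hard to recover later.

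**Working it through.** **Is there a stated figure to reproduce?** Not for adherence: the article gives no expected attendance rate and no cut-off. The nearby recruitment figures do reproduce (6 months × 10 = 60; 60 × (1 − 0.30) = 42 completers), but this point does not depend on them.

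**Step 1. How much the SEC cut-off matters.**

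Inputs: 8 classes (SEC section). The attendance probability per class, p, is my assumption, with 0.7 as the central value and 0.5 to 0.8 as the range.

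With independent sessions, the share classed as adherent at cut-off c is

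P(X ≥ c) = Σ from k = c to 8 of C(8,k) p^k (1 − p)^(8 − k).

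At p = 0.7:

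- 8 of 8: 0.7^8 = 0.058
- ≥7: 0.058 + 8 × 0.7^7 × 0.3 = 0.058 + 0.198 = 0.26
- ≥6: adding 28 × 0.7^6 × 0.3^2 = 0.296 gives 0.55
- ≥5: adding 56 × 0.7^5 × 0.3^3 = 0.254 gives 0.81
- ≥4: adding 70 × 0.7^4 × 0.3^4 = 0.136 gives 0.94

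Real attendance clusters within people: some attend nearly everything, others stop early. A beta-binomial with an assumed within-person correlation of 0.4 has parameters summing to 1/0.4 − 1 = 1.5, that is 1.05 and 0.45 at p = 0.7.

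| Cut-off (of 8) | Independent, p = 0.5 | Independent, p = 0.7 | Independent, p = 0.8 | Clustered, p = 0.7 |
|---|---|---|---|---|
| ≥4 | 64% | 94% | 99% | 77% |
| ≥5 | 36% | 81% | 94% | 70% |
| ≥6 | 14% | 55% | 80% | 61% |
| ≥7 | 4% | 26% | 50% | 50% |
| 8 | 0% (rounded) | 6% | 17% | 34% |

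At p = 0.7 the choice of cut-off alone moves the rate by 94 − 6 = 88 percentage points with independent sessions, and by 77 − 34 = 43 points with strong clustering.

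For scale, equal allocation (assumed, as the ratio is not stated) gives 60/3 = 20 per arm. An observed 14 of 20 adherent has an exact 95% confidence interval of 46% to 88%, a width of 42 points. Freedom to choose the cut-off is therefore at least as large as the sampling uncertainty, and no confidence interval would show it.

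**Step 2. The walking programme.** Four diary quantities are listed (frequency, distance, steps, duration) with no rule for which one counts or how they combine. Both the metric and the cut-off are open. The recording instructions in the same section name walk frequency, walk duration and steps, but not distance. No proportion can be calculated without inventing the metric.

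**Step 3. The control arm.** Adherence as a proportion needs visits attended divided by visits planned or booked. The numerator is recorded. No denominator is specified, and 5.8 is an expected mean, not a prescription. Take two hypothetical patients:

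- Patient A recovers and is discharged as planned after 2 of 2 booked visits: count 2, ratio 2/2 = 100%.
- Patient B misses half of 12 booked visits: count 6, ratio 6/12 = 50%.

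The count ranks B above A, while the ratio ranks A above B.

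**Step 4. Where the cut-offs enter the plan.** The Data Analysis section tabulates adherence levels. It states no analysis restricted to adherers, and Controlling bias names intention-to-treat. The non-feasibility sign that mentions adherence is worded as participant feedback, not as a rate derived from the cut-offs.

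**The case against.** A good deal can be said for the plan.

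- **Feasibility is not made to depend on the cut-offs.** A reader might infer that adherence decides whether a main trial goes ahead, so that the investigators could set the threshold to pass or fail. The article does not support this. Adherence appears as participant feedback, within one of three signs, and nothing ties that sign to the deferred cut-offs. This part of the objection stands in full.
- **No planned estimate uses the cut-off.** Treatment effects, effect sizes and the power calculation for the main trial do not involve it. This also stands, and it limits the seriousness.
- **Learning a workable definition is a proper feasibility aim.** The objectives include piloting procedures and refining the protocol, and the deferral is openly stated. If full counts are shown, a reader can apply any cut-off. This stands as a reason to explore definitions. It is no reason to have none stated beforehand, since the class count and the walking aim are already written down.
- **No comparison of adherence between arms is planned.** A reader might complain that adherence cannot be compared across the three arms, or ask for one common metric. The between-group objective does not list adherence, and the interventions differ in kind. Scoring the walking arm on calls answered and diaries returned would ignore the walking itself. Arm-specific measures are reasonable.
- **The treatment record forms are not shown.** Missed visits and type of discharge may already be on them. That stands, so the request below is conditional. The article's stated adherence measure for UP is still the bare count.

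**Conclusion.** The point holds in a limited form. The article commits to choosing the SEC and WP adherence cut-offs after the trial, with outcomes known and the assessor unblinded. It also labels as adherence a control-arm count that measures treatment received.

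Followed as written, the plan gives an active-arm adherence rate that depends on the data. In the SEC illustration the same attendance could be reported as anything from 94% to 6% adherent, or from 77% to 34% with strong clustering. Those figures rest on assumed 70% attendance, an assumed correlation of 0.4 and cut-offs from 4 to 8 classes. They show sensitivity and are not forecasts. For UP no adherence proportion can be formed from the stated measure.

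The effect is on how adherence is reported and understood when the main trial is designed. Sample size, power and the planned treatment estimates are unaffected. It should be corrected, and doing so is cheap.

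**What to change.** 1. **SEC and WP.** Before any 3-month data are examined, state an adherence definition for each arm. For SEC, express it as classes attended out of 8. For WP, express it as diary-recorded walking against the programme's own stated aim, with a rule saying which of the four diary quantities counts. The investigators should choose the cut-offs; what matters here is that they are written down first.
2. **Reporting.** Give the full distribution of attendance and diary quantities in each arm. Label any other cut-off explored for the main trial as post hoc.
3. **UP.** Assess adherence as visits attended out of visits booked. Record planned discharge versus self-discharge on the existing treatment record form, if it is not already captured. Report the raw visit count separately, as treatment received.

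The cost is a few sentences and at most one or two fields on a form that clinicians already complete for every patient. The downside is being held to a cut-off that may prove awkward, which the full distributions and labelled exploratory cut-offs largely offset. No common metric across arms is needed, and the sample size does not change.
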